#### Radiologic outcomes for the diagnosis of appendicitis

• Diagnostic performance

 ➢ Area under receiver-operating-characteristic curve

• Diagnostic confidence

 ➢ Likelihood score for appendicitis in patients confirmed as having appendicitis

 ➢ Likelihood score for appendicitis in patients confirmed as not having appendicitis

### Reference standards

For participants undergoing abdominal surgery, the final diagnosis is made using the surgical and pathologic findings. Pathologic examinations of surgical specimens are performed by site pathologists during daily practice [41]. For participants not undergoing surgery, the outcome assessors will determine the final diagnosis based on the medical records and a standardized telephone interview conducted 3 months after the initial presentation. The outcome assessors are emergency department physicians or radiologists blinded to the allocation.

The histopathologic diagnosis of acute appendicitis is defined as neutrophil infiltration of the appendiceal wall [41]. If neutrophilic collections are confined to the mucosa, the diagnosis of acute appendicitis is based on the presence of mucosal ulcerations [42]. A diagnosis of appendiceal perforation is based on spillage of the appendiceal contents, peritonitis or an abscess observed during surgery [43], or a pathologically confirmed appendiceal wall defect due to transmural necrosis.

### Sample size

We assume 4% NAR following SD CT based on previous data from some of the sites [24,26,44]. The same NAR is assumed following LD CT. We judge 8.5% NAR to be clinically acceptable following LD CT, which corresponds to a non-inferiority margin of 4.5 percentage points, considering the potential reduction in carcinogenic risk associated with CT. With these assumptions and a 10% dropout rate, 444 non-incidental appendectomies per group are needed to obtain 90% statistical power with two-sided α = 0.05.

It should be recognized that participants not undergoing appendectomy are also included in LOCAT, although the required sample size was determined in terms of the number of appendectomies. Given that appendectomy is eventually performed in 40% to 44% of the patients undergoing appendiceal CT [24-26], we assume that appendectomy will be eventually performed in at least 30% of all LOCAT participants, considering the variability across sites. With this assumption, the total number of participants included in LOCAT is approximately 3,000.

If two or more life-threatening or fatal [45] serious adverse events (SAEs) are reported in any of the two groups, then LOCAT will be suspended and the Coordinating Committee will investigate if the events are attributable to study procedures and determine whether or not LOCAT should be terminated early.

### Analysis

All participants undergoing randomization will be included in the analysis in the groups to which they are originally assigned. While the intention-to-treat analysis will be used primarily, an additional per-protocol analysis will be performed. The NARs for both groups and the two-sided 95% CI for the differences will be calculated. The non-inferiority of LD CT compared to SD CT will be accepted if the upper bound of the two-sided 95% CI lies below the non-inferiority margin, which is 4.5 percentage points.

A similar non-inferiority analysis will be performed for APR with a non-inferiority margin of 10.0 percentage points. Chi-square tests, Fisher’s exact tests, Mann–Whitney U tests and receiver-operating-characteristic analysis (non-parametric Wilcoxon statistic) will be used to compare the other secondary end points. A two-sided *P* < 0.05 indicates statistical significance. If the study results show considerable variation across sites, generalized estimating equations will be used to account for the clustering effect by site.

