### Randomization

Participants who give informed consent will be randomly assigned to either LD or SD CT at a 1:1 ratio. Details of stratification and blocks are confidential. Sequentially numbered opaque sealed envelopes containing computer-generated random assignments will be prepared for each site. Randomization will take place at the time of the CT examination. To enter a participant into LOCAT, the radiology technologist on duty will open the next consecutively numbered envelope.

While it is not possible to blind the medical staff to the allocation because of obvious differences in image texture (dependent on the CT radiation dose), the participants and independent outcome assessors will be kept blinded to the allocation.

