### Negative appendectomy rate versus appendiceal perforation rate as the primary end point

The primary end point is NAR and the most important secondary end point is APR. This is because NAR and APR are the two most important established reciprocal measures of quality of care [53] in the diagnosis of appendicitis. They represent the consequences of false-positive and delayed diagnoses, respectively. An inverse relation likely exists between NAR and APR if the overall performance of a diagnostic system is maintained stably. It has been asserted that a certain level of NAR (which was up to 20% before the introduction of CT) is an appropriate index of management and that a failure to maintain this surgical threshold is an indication of insufficient surgical aggressiveness and of an excessive rate of delayed diagnosis.

If LOCAT can prove the non-inferiority of LD CT compared to SD CT in terms of APR as well as NAR, the LOCAT results will be more conclusive than only proving the non-inferiority of NAR, in establishing LD CT as the first-line imaging test. Nevertheless, we have decided not to include APR as a co-primary end point for a number of reasons. First, ambiguity exists in defining appendiceal perforation as will be discussed later, which may partly explain the wide variation in reported APRs in previous studies [39] and across the sites in a retrospective study ([name] on behalf of the LOCAT group: Diagnostic imaging utilization in cases of acute appendicitis: multi-center experience, unpublished). Second, while NAR explicitly represents the clinical consequences of false-positive diagnoses, APR is not so directly linked with false-negative diagnoses, as APR is also affected by many other factors including disease severity at the time of presentation and non-medical factors that delay treatment [54]. Third, appendiceal perforation, especially in a mild form, does not always affect clinical outcomes. Therefore, we have selected a single primary end point, NAR, in LOCAT.

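### Whether site enters the primary non-inferiority interval depends on an undefined trigger read from the results; one site-stratified interval should be fixed in advance

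*Protocol article*

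**What the plan says.** Under Analysis, the default is a plain comparison: "The NARs for both groups and the two-sided 95% CI for the differences will be calculated". Non-inferiority "will be accepted if the upper bound of the two-sided 95% CI lies below the non-inferiority margin, which is 4.5 percentage points". A similar analysis is planned for the appendiceal perforation rate (APR), with a 10-point margin. After the list of tests for the other secondary end points comes the rule at issue: "If the study results show considerable variation across sites, generalized estimating equations will be used to account for the clustering effect by site".

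Under Randomization, allocation is individual: "Participants who give informed consent will be randomly assigned to either LD or SD CT at a 1:1 ratio". It is run site by site: "Sequentially numbered opaque sealed envelopes containing computer-generated random assignments will be prepared for each site". The same section adds: "Details of stratification and blocks are confidential". The article gives no number of sites.

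**The concern.** The rule leaves four things open: how variation is measured, how much of it triggers the switch, which end points it covers, and which interval is then held against 4.5 points. If it covers NAR, the interval that decides the trial's single primary claim can come from either of two methods, chosen on the results. The fixed-sequence scheme in the Discussion tests APR only after NAR succeeds, so the same choice also opens or closes the key secondary claim.

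The fallback method matters too. GEE clustered on site relies on a sandwich variance that tends to be too small when clusters are few, and the article mentions no correction. Events are sparse: with 400 appendectomies per arm, NARs of 4% and 8.5% mean 400 × 0.04 = 16 and 400 × 0.085 = 34 negative appendectomies.

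Nothing needs to be learned from the results before deciding how to treat site. Envelopes are prepared per site, and the article already expects sites to differ in the proportion having appendectomy (Sample size), in APR (Discussion) and in radiation dose (Discussion).

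**Working it through.** **The plan's own figure.** Inputs from Sample size: NAR 4% in both groups, margin 4.5 points, two-sided α 0.05, power 90%, dropout 10%.

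n = (1.960 + 1.282)² × 2 × 0.04 × 0.96 / 0.045² ≈ 399 per group; 399 / 0.9 = 443.3, rounded up to 444. The stated figure reproduces.

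**Simulation at the margin.** True NARs were 4% (standard dose) and 8.5% (low dose), with about 400 appendectomies per arm and equal allocation within site. A trial counts as a false non-inferiority when the upper 95% limit is below 4.5 points; the nominal rate is 2.5%. Assumptions not in the article: 10, 20 or 30 sites, between-site SD of NAR of 0-4 points, and no treatment-by-site variation. Each scenario had 20,000-40,000 trials. The Monte Carlo standard error at 20,000 is √(0.025 × 0.975 / 20,000) = 0.11 points.

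Methods, for sites k = 1…K with D = p₁ − p₀:
- Unadjusted: SE² = p₀(1−p₀)/N₀ + p₁(1−p₁)/N₁.
- GEE (identity link, independence, uncorrected sandwich): same D, with SE² = Σ u_k², where u_k = (y₁k − n₁k p₁)/N₁ − (y₀k − n₀k p₀)/N₀.
- Corrected GEE: that SE × √(K/(K−1)), with a t quantile on K−1 df. At 10 sites the multiplier is 2.262 × 1.054 = 2.38 instead of 1.96; at 30 sites it is 2.045 × 1.017 = 2.08.
- Mantel-Haenszel: Σ[(y₁k n₀k − y₀k n₁k)/n_k] / Σ[n₀k n₁k/n_k], with Sato variance.

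| False non-inferiority, % | 10 sites | 20 sites | 30 sites |
|---|---|---|---|
| Unadjusted | 2.6-3.0 | 2.6-3.1 | 2.6-3.0 |
| Mantel-Haenszel by site | 2.6-3.0 | 2.7-2.9 | 2.8-2.9 |
| GEE always, uncorrected | 5.0-5.8 | 3.7-4.5 | 3.4-4.1 |
| GEE always, corrected | 2.6-2.9 | 2.6-2.8 | 2.7-2.9 |
| Uncorrected GEE if site test P<0.05 | 3.0-5.1 | 2.9-4.1 | 2.8-3.5 |
| Unadjusted or uncorrected GEE, whichever passes | 5.5-6.3 | 4.2-5.1 | 3.7-4.5 |

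The Mantel-Haenszel and corrected-GEE rows use equal site sizes; the others cover equal and unequal sizes.

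A separate run with 8-30 unequal sites and a trigger at P<0.10 gave 2.7-3.1% unadjusted, 2.7-3.1% Mantel-Haenszel, 4.0-6.4% uncorrected GEE, 3.0-5.1% for the triggered switch and 4.4-6.9% for free choice.

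**The trigger.** A treatment-by-site test as trigger gave 2.4-2.9%, so the choice of measure that the article leaves open changes the result. With equal sites, a 5% site test fired in 15-26% of trials at a between-site SD of 2 points and in 59-70% at 4 points.

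**Power** (true difference 0, SD 2 points; 10, 20, 30 sites): unadjusted 90.3, 91.3, 91.0%; Mantel-Haenszel 90.2, 91.0, 90.4%; corrected GEE 83.3, 88.5, 89.0%.

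**If the treatment effect itself varies by site (SD τ).** The unadjusted rate is Φ(−1.96 × SE / √(SE² + τ²/K)), with SE² = (0.04 × 0.96 + 0.085 × 0.915)/400 = 0.000290. At τ = 2 points it is 3.3, 2.9 and 2.8% for 10, 20 and 30 sites. Reaching 5% needs τ of about 3.5, 4.9 and 6.0 points.

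**The case against.** A reader might infer that leaving site out of the default analysis inflates the error. It does not. Randomisation is individual and balanced within site, so differences in NAR level fall equally on both arms. The unadjusted and stratified intervals have practically the same error rate and power, and this part of the objection stands in full.

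A reader might also infer that the rule doubles the error rate. The article states no link, working correlation or variance estimator for GEE, and may leave these to a fuller document. With a leverage-corrected sandwich and t on K−1 df, the heterogeneity-triggered switch gives 2.5-3.1% for 8-40 sites, and picking the more favourable of the unadjusted and corrected intervals gives 3.4-3.9%. Invitations went to members from 119 hospitals, so many sites are possible; with an uncorrected variance the triggered switch at 30-40 sites gives 2.9-4.2%. The sentence is also a one-way conditional rule, which is not a stated licence to pick the better result. All of this stands and limits the size of the concern.

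Nor does the article show that the switch is likely for NAR. The variation that it reports concerns other quantities, for example "wide variation in reported APRs in previous studies [39] and across the sites in a retrospective study". It does not say that variation would be judged by arm; pooled site rates could be inspected without the allocation. The sentence follows the secondary end points and may have been meant for them only.

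What does not follow is that the point is merely detail left to an analysis plan. The article states a conditional rule, words it for the study results without limit, and gives no criterion for applying it. If only secondary end points were meant, it should say so.

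**Conclusion.** The concern holds in a limited form. The handling of site depends on the results through an undefined criterion, and the text does not say which interval would then decide non-inferiority. Against a nominal 2.5%, and without treatment-by-site variation, the rate is about 3-5% for a heterogeneity-test trigger with an uncorrected sandwich variance, and about 4-7% if the favourable method could be chosen. Both ranges assume 8-30 sites. Reaching double the nominal rate takes few sites together with an uncorrected variance (a large spread in NAR under a fixed trigger, or a free choice of method), or a treatment effect that varies strongly between sites.

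The default analysis is sound and the sample size is correct. This is an inexpensive improvement to the plan. The documents do not support calling it an error that undermines the primary analysis.

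**What to change.** Replace the conditional sentence with one rule along these lines:

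*The NAR difference and the APR difference, each with a two-sided 95% CI, will be estimated with site as a stratum (Mantel-Haenszel or stratified Miettinen-Nurminen risk difference), whatever variation between sites is observed. Small sites will be pooled by a rule fixed before unblinding. These intervals decide non-inferiority. Variation between sites in the difference between groups will be described. GEE clustered on site, with a small-sample-corrected variance, is a sensitivity analysis only.*

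Stratification does not protect against a treatment effect that varies by site: with 10 sites, NAR SD 2 points and τ = 3.5 points, the Mantel-Haenszel rate is 5.6% and the corrected-GEE rate 3.9%. That is a reason to keep the corrected GEE as a sensitivity analysis in a trial that aims at generalisability. Using it as the primary method would cost power if sites are few (83% at 10).

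The change is to analysis wording only. It needs no patients and no new data, since site is known from the envelope series, and it discloses no block sizes. The 444 per group and about 90% power stay as they are. It should be settled before unblinding, because afterwards the choice of method could not be shown to be independent of the results.

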## Discussion

Here we elaborate on several challenging or potentially debatable components of the LOCAT design, which we believe will be useful to other investigators designing or implementing a trial on the diagnosis of appendicitis.

### Broad eligibility criteria

LOCAT uses broad eligibility criteria to reflect normal practice at the sites and presumably in many other institutions where physicians maintain a reasonably sensitive standpoint in raising a clinical suspicion of appendicitis and then use imaging tests to confirm or rule out appendicitis.

First, the clinical suspicion for appendicitis will be left to the discretion of the emergency department physicians on duty. While a clinical suspicion for appendicitis is generally raised by known symptoms and signs including right lower quadrant pain, migration of pain, vomiting, tenderness and/or rigidity [46], we have chosen not to list any specific clinical criteria for defining the ‘suspicion for appendicitis’ in LOCAT. In general, patients with appendicitis have diverse presentations [47-49] and clinical assessments unavoidably require many physicians with different expertise, due to the high prevalence of the disease. Therefore, the adoption of any fixed clinical criteria may compromise the generalizability of the study findings. Wagner *et al*. [46] reviewed ten previous ‘high-quality’ studies and found that all of the studies used inclusion criteria of ‘suspected appendicitis’ or ‘abdominal pain’ without further definition. This is understandable, as fixing clinical criteria to investigate diagnostic clinical features is prone to circular logic.

Second, the need for a CT examination will also be left to the discretion of the emergency physicians on duty. While it may be debatable in Western countries [50] whether patients with typical presentations of appendicitis require a preoperative imaging test or not, such patients mostly undergo a CT examination in Korea where right-sided colonic diverticulitis, which often clinically mimics typical appendicitis [51,52], is a common alternative diagnosis [26]. While the need for a CT examination should be individualized for each patient, the decision threshold to utilize CT as the initial imaging modality may not be uniform among sites or emergency department physicians [2,50]. Although previous investigators have tried to divide the indication for performing a CT examination into two thresholds of atypical versus all suspected (including both typical and atypical) patients, a meta-analysis [50] has suggested that the dichotomy of atypical versus typical presentations is merely theoretical. Because of the broad eligibility criteria in LOCAT, patients with either typical or atypical presentations can be enrolled [3,50].

### Negative appendectomy rate versus appendiceal perforation rate as the primary end point

The primary end point is NAR and the most important secondary end point is APR. This is because NAR and APR are the two most important established reciprocal measures of quality of care [53] in the diagnosis of appendicitis. They represent the consequences of false-positive and delayed diagnoses, respectively. An inverse relation likely exists between NAR and APR if the overall performance of a diagnostic system is maintained stably. It has been asserted that a certain level of NAR (which was up to 20% before the introduction of CT) is an appropriate index of management and that a failure to maintain this surgical threshold is an indication of insufficient surgical aggressiveness and of an excessive rate of delayed diagnosis.

If LOCAT can prove the non-inferiority of LD CT compared to SD CT in terms of APR as well as NAR, the LOCAT results will be more conclusive than only proving the non-inferiority of NAR, in establishing LD CT as the first-line imaging test. Nevertheless, we have decided not to include APR as a co-primary end point for a number of reasons. First, ambiguity exists in defining appendiceal perforation as will be discussed later, which may partly explain the wide variation in reported APRs in previous studies [39] and across the sites in a retrospective study ([name] on behalf of the LOCAT group: Diagnostic imaging utilization in cases of acute appendicitis: multi-center experience, unpublished). Second, while NAR explicitly represents the clinical consequences of false-positive diagnoses, APR is not so directly linked with false-negative diagnoses, as APR is also affected by many other factors including disease severity at the time of presentation and non-medical factors that delay treatment [54]. Third, appendiceal perforation, especially in a mild form, does not always affect clinical outcomes. Therefore, we have selected a single primary end point, NAR, in LOCAT.

Nevertheless, non-inferiority testing will be performed for APR as well as NAR. While testing two different hypotheses simultaneously (one for NAR and the other for APR) generally requires the control of Type I errors, we will use a hierarchical approach that can be used to test ordered hypotheses without the need for an α adjustment [55]. This fixed-sequence testing will allow the non-inferiority hypothesis for APR to be tested only if the non-inferiority for NAR is established first.

### Advanced CT imaging techniques

There have been remarkable advances in CT technology over the last decade, including improved spatial resolution, higher signal-to-noise ratio, faster scanning, increased use of multiplanar images and the introduction of the sliding slab averaging technique. Therefore, for the same radiation dose, the CT imaging protocol in LOCAT is considered to be better for visualizing the appendix than the CT protocols employed in the previous studies, which measured the effect of preoperative CT on NAR [6,8-12].

For example, thin-section (≤2 mm) image datasets, in addition to conventional thick-sections (3 to 5 mm), should be available to the radiologists. These can be reviewed using the multiplanar sliding slab averaging technique. The two-tier (thick and thin) image reconstruction technique [56] and the sliding slab averaging technique [36-38] can enhance visualization of the appendix [24-26,31,57,58], potentially compensating for the lower quality of LD CT images. The importance of these techniques is often overlooked by radiologists, although many ordinary hospitals now have sufficient hardware and network resources to implement them.

### Radiation dose

CT is rapidly evolving. Because participant recruitment for LOCAT will take several years, sites are allowed to implement advances during the course of LOCAT so that CT imaging parameters remain as up to date as possible. Within the study protocol, changes to the imaging protocol, even including the radiation dose level (target DLP) for the SD group, are allowed during the study period.

There is considerable variation across the sites in the radiation doses conventionally used to diagnose appendicitis ([name] on behalf of the LOCAT group: Diagnostic imaging utilization in cases of acute appendicitis: multi-center experience, unpublished). In addition, the standard-of-care radiation doses may gradually decrease to some extent during the study period, through advances in CT technology and greater awareness of the associated carcinogenic risk [35]. Taking into consideration these variations and changes, LOCAT has a unidirectional standpoint in determining and adjusting radiation doses: it is flexible regarding dose decreases in either group while being strictly against dose increases. For example, the principle for dose calibration is as follows. If the median DLP for a number of participants exceeds a predefined target by 10% then the dose adjustment is mandatory, while it is left to the discretion of the site PI whether or not to adjust for the reverse error. It should be noted that lowering the SD during the course of LOCAT will affect the study results toward the non-inferiority. Nevertheless, this policy is in line with the ultimate goal of the LOCAT Group, which is to disseminate the use of the LD CT technique throughout the sites and other hospitals over the course of LOCAT.

